| Late clinical or parasitologic failure (% per-protocol) | 0 (0) | 50 (57) |
| Outcomes unknown | 25 | 18 |
| Total | 105 | 105 |

Table 1: Outcomes of 28-day efficacy study of chloroquine vs. SP for the treatment of uncomplicated malaria among children in Blantyre, Malawi.

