## Definition of treatment outcomes

The 2004 WHO definitions of treatment outcomes will be used as follows:

Therapeutic efficacy will be defined as:

- Early treatment failure (any one of the following)
  - danger signs or severe malaria on days 1, 2 or 3, with parasitemia. Hemoglobin less than 5 without any other signs of severe disease when a participant is receiving therapy will not be a criteria for Early Treatment Failure as hemoglobin levels frequently decrease even with effective therapy.
  - parasitemia on Day 2>Day 0 level
  - axillary temperature > 37.5oC on day 3 in the presence of parasitemia
  - parasitemia on day 3 > 25% of day 0 level
- Late clinical failure
  - development of danger signs, severe malaria or axillary temperature > 37.5oC or a history of fever within the past 24 hours in the presence of parasitemia during days 4-28
  - and no criteria for early treatment failure
- Late parasitologic failure
  - Presence of parasitemia on day 28 without fever
  - and without previously meeting any of the criteria for early treatment or late clinic failure
- Adequate clinical and parasitologic response
  - absence of parasitemia on day 28
  - and without previously meeting any of the criteria of early treatment or late clinical failure

A new episode of malaria will refer to any episode of clinical malaria (symptoms and a positive malaria smear) that occurs more than 14 days after therapy.

If a seizure meets the following criteria of a febrile seizure, the episode will not be considered a danger sign. The following criteria must be met:

1. Occurring in the presence of a reported or documented fever or with a rise in temperature.
2. Generalized seizure witnessed by reliable family member or study staff
3. Duration ≤30 minutes
4. Absence of mental status impairment two hours after the event..
5. Normal neurological examination by a study clinician or investigator within 24 hours of seizure.

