## Final Analysis Plan

The final analysis of the primary objective will be a comparison of incidence rates of malaria treatment episodes per year of follow-up (not including the first infection occurring at enrollment) in each arm of the study. The rates and 95% confidence intervals will be calculated using Poisson distribution. Reported antimalarial drug use without documented positive malaria smear will not count as a malaria treatment episode. Malaria episodes treated with non-study medicines at Queen Elizabeth Central Hospital with verified positive malaria smears will be counted as malaria treatment episodes, and any such treatments will be compared among groups to rule out bias due to different rates of non-study treatment. Withdrawal of participation is described above and includes participants who miss ≥ 2 consecutive routine follow-up visits. For the primary study endpoint, follow-up time for participants while they are enrolled in the study will be included in the analysis. For participants who were withdrawn after missing > 2 consecutive follow-up visits, time after the last visit will be censored from incidence analysis.

Drug efficacy for the first and subsequent episodes of malaria will be compared using Kaplan-Meier 28-day survival estimated and compared using Cox proportional hazards regression. Per-protocol analysis will be used to compare treatment efficacy, with data excluded from treatment episodes for which treatment outcome cannot be determined. Survival analysis will also be used to assess time to first resistant infection in each arm. Categorical data including episodes of liver, kidney or neurological toxicity and presence of anemia will be compared using 2 analysis. Logistic regression will be used to adjust for covariates.

Survival analysis will be used to assess the role of travel outside of Blantyre and bed net use on the risk for malarial and time to first malaria episode. This analysis will be conducted both with and without the inclusion of treatment arm as a covariate in the analysis.

Data will be entered in to the database on the computers at the field site. On a daily basis, the data will be transferred via the internet to the EMMES corporation web-based system.

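### The 28-day Kaplan-Meier and Cox efficacy analyses drop episodes with an undetermined outcome instead of censoring them, which under random loss overstates failure or leaves it unchanged

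*Protocol*

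**What the plan says.** The Protocol's Final Analysis Plan (section 11.3) states: "Drug efficacy for the first and subsequent episodes of malaria will be compared using Kaplan-Meier 28-day survival estimated and compared using Cox proportional hazards regression". The next sentence adds: "Per-protocol analysis will be used to compare treatment efficacy, with data excluded from treatment episodes for which treatment outcome cannot be determined".

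Definition of treatment outcomes (section 4.3) shows which episodes can be undetermined:

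- Early treatment failure includes "danger signs or severe malaria on days 1, 2 or 3, with parasitemia". It is settled when seen.
- Late clinical failure is a clinical event "in the presence of parasitemia during days 4-28". It is also settled when seen.
- Late parasitologic failure is "Presence of parasitemia on day 28 without fever". It can be seen only at the last visit.
- Adequate response requires "absence of parasitemia on day 28". It too can be confirmed only at the last visit.

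Table 1 in Background Information reports the site's 2005 study of chloroquine against SP, with 105 children per arm. It has the row "Outcomes unknown | 25 | 18" (chloroquine, then SP), and its percentages are per-protocol.

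**The concern.** Kaplan-Meier and Cox methods exist so that a child seen well until day 14 and then lost still counts as at risk until day 14. The exclusion rule removes that child. A child who fails clinically on day 10 and is lost on day 14 has a determined outcome and stays in. Inclusion therefore depends partly on the outcome.

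Once undetermined episodes are gone, every remaining episode has either failed or reached day 28. No censoring for loss is left, and for the all-cause outcome the day-28 Kaplan-Meier estimate equals the per-protocol proportion.

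At stake are secondary objectives 1 and 2, efficacy at first and at later administrations. If undetermined outcomes are more common in one arm, part of any efficacy contrast could come from the rule. Unequal loss is plausible: the trial is open label, and only the combination arms have a second drug-administration step with its own vomiting sequence (Drug administration).

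**Working it through.** **Reproducing Table 1.** With unknown outcomes removed:

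- Chloroquine: 105 − 25 = 80 determined. Success 79/80 = 98.75%, failure 1/80 = 1.25%.
- SP: 105 − 18 = 87 determined. Success 16/87 = 18.4%, early failure 21/87 = 24.1%, late failure 50/87 = 57.5%.

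These agree with the printed 99 and 1, and 18, 24 and 57, to within rounding. The unknown shares are 25/105 = 23.8%, 18/105 = 17.1% and, pooled, 43/210 = 20.5%.

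**Censoring the same episodes.** Table 1 gives no dates of loss, so only a range follows.

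- Chloroquine failure is 1/105 = 0.95% if all losses came after the one early failure, and 1/80 = 1.25% if all came before it. The per-protocol figure is 1.25%.
- SP failure is 71/105 = 67.6% if all losses came after all failures. If losses fell between the early and late failures, it is 1 − (84/105) × (16/66) = 80.6%. The per-protocol figure is 71/87 = 81.6%.

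**General effect under random loss.** Let p be the true 28-day failure risk, d the probability of loss before day 28 and g the chance that a child who would fail is seen to fail before being lost. The exclusion rule estimates

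p·g / [p·g + (1 − p)(1 − d)].

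Three failure timings span the range:

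- all failures before any loss: g = 1;
- failures and losses both uniform over 28 days: g = 1 − d/2;
- all failures on day 28: g = 1 − d.

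For p = 5% and d = 20.5%, (1 − p)(1 − d) = 0.95 × 0.795 = 0.75525:

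- early: 0.05 / (0.05 + 0.75525) = 6.2%;
- uniform: 0.044875 / (0.044875 + 0.75525) = 5.6%;
- day 28: 0.03975 / (0.03975 + 0.75525) = 5.0%.

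| True failure | Early | Uniform | All on day 28 |
|---|---|---|---|
| 1% | 1.3% | 1.1% | 1.0% |
| 5% | 6.2% | 5.6% | 5.0% |
| 10% | 12.3% | 11.1% | 10.0% |

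(All rows at d = 20.5%.) When failure is rare, the relative excess cannot go above about 1/(1 − d) = 1/0.795 = 1.26.

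A simulation of 400,000 episodes with uniform timing, p = 5% and d = 20.5% gave 5.0% for Kaplan-Meier with censoring and 5.6% with exclusion.

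**Unequal loss.** Take p = 5% in both arms, the same failure timing, and loss of 17% against 23.8%:

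- early: 5.96% against 6.46%, a difference of 0.50 points;
- uniform: 5.48% against 5.74%, a difference of 0.25 points;
- day 28: 5.0% in both, no difference.

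**The case against.** **The sentence may describe a separate proportion.** Secondary Outcome Measures (section 3.2.2) names a rate of adequate response at 28 days, and the per-protocol sentence could refer to that alone. This is possible but strained. The two sentences are consecutive and both describe comparing efficacy, and nothing limits the exclusion to a proportion. Even on that reading, the text needs to say so.

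**The effect is small.** This stands. Sample Size Considerations expects chloroquine efficacy above 95% and says day-28 differences are unlikely to be found. With 160 per arm and 5% failure, the standard error of a difference is √(2 × 0.05 × 0.95 / 160) = 2.4 points, about five times the largest spurious difference computed above.

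**The 2005 rates may not carry over.** This also stands. Table 1 gives no reason for the unknown outcomes, and SP is not an arm of this trial. Its 17% is not a clean probability of loss either, since 71 of 105 SP children had already failed. A reader might infer that a fifth of this trial's data will be discarded; the document supports that only as a projection.

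**Failures can be undetermined too.** A reader might infer that only non-failures are excluded, so failure must be overstated. Section 4.3 does not support this, because loss before day 28 also hides failures that would have appeared on day 28. For PCR-corrected efficacy, Molecular analysis (section 8.4) allows an indeterminate genotype, so an observed recurrence may lack a determined outcome. What holds is narrower: for the all-cause outcome, an episode is undetermined only if no failure has been observed.

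**Conclusion.** The exclusion rule conflicts with the survival analysis it accompanies and should be changed. Under random loss it overstates all-cause failure or leaves it unchanged, with no bias if every failure appears on day 28. At 20.5% loss and 5% true failure, the excess is 0 to 1.2 percentage points. Loss of 17% against 24% adds at most about 0.5 points between arms with equal failure risk and timing. These figures assume that loss resembles the 2005 study and is unrelated to outcome; if loss depends on outcome, the direction is not fixed.

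The primary endpoint is not affected. The same section counts follow-up while children are enrolled and censors time after the last visit for those withdrawn for missed visits.

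A reader might also infer that repeat episodes in one child will be treated as independent. The protocol does not say so. It is silent on within-child correlation, which is commonly left to the SAP, so that is no finding here.

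**What to change.** Replace the per-protocol sentence in the Final Analysis Plan with wording to this effect: all treated episodes enter the Kaplan-Meier and Cox analyses; an episode whose outcome cannot be determined is censored at the last visit with a smear result; the per-protocol proportion is reported as a supportive summary.

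The cost is a change of wording. No new visit, sample or data item is needed, because smears are already scheduled at each efficacy visit. The per-protocol figure stays available for comparison with other 28-day studies. Censoring removes the bias under random loss, but not bias from loss that depends on outcome.

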We have selected three partner drugs to use in combination with chloroquine in order to determine the pharmacokinetic and pharmacodynamic properties that most optimally protect against the emergence or re-emergence of chloroquine resistance. Artesunate is a highly effective, but very short acting, medication that will decrease parasite biomass rapidly but will no longer have any activity in the blood one day after therapy. Azithromycin is slow acting in its antimalarial activity, but remains at a high level in the blood for approximately 5-10 days after therapy, based on data from bacterial infection. It is a moderately effective antimalarial. Finally, atovaquone, in the AP coformulated Malarone, has a very prolonged terminal elimination phase and likely approximates the terminal half-life of chloroquine. Although its pharmacokinetic properties are similar to azithromycin, its pharmacodynamic properties are different, i.e., it is a more effective drug, so we expect that antimalarial activity will be maintained as the drug level gradually decreases. The specific combinations being tested may not be optimal for eventual deployment, but all combinations are likely to be safe and highly efficacious. Rather, we hope to answer the question: for how long does a partner drug need to be active to protect against resistance? The results of this study will thus inform the rational design of the next generation of combination therapies.

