### Secondary Outcome Measures

1. To assess the antimalarial drug efficacy at first administration, by treatment arm.

- Rate of adequate clinical and parasitologic response 28 days after initial malaria

The 28 day outcomes represent the standard assessment of antimalarial efficacy and provide important information about the short term benefits of the drug. Since we will assess the ability of combination therapy to protect against the emergence of resistance, we are most interested in clinically apparent, in vivo drug efficacy.

- The incidence of new infections and recrudescent infections after initial treatment in each treatment arm

Parasites that emerge after treatment may be classified as new infections (arising from a new exposure) or recrudescent infections (arising from the original infection). Drugs that have poor efficacy but long half-lives may protect against new infections, but fail to cure the original infection completely. In contrast, shorter acting but highly effective medications may treat the initial infection successfully, but leave the individual susceptible to new infections in areas of high transmission. Distinguishing these two mechanisms will help to elucidate the complex interaction between the drugs and the parasite population.

1. To assess the antimalarial drug efficacy during subsequent episodes of malaria, by treatment arm.

- Rate of adequate clinical and parasitologic response 28 days after subsequent new episodes of malaria
- The incidence of new infections and recrudescent infections after subsequent new episodes of malaria

The same outcomes measured after the first administration will be monitored for subsequent administrations. This ability to detect efficacy after repeated use is a strength of the longitudinal study design.

- Incidence of severe malaria

Although children who present with severe malaria will be excluded from enrollment in the study, subsequent episodes of severe disease in study participants will be assessed as study endpoints. We would expect severe malaria to be rare in this population when children are treated promptly and effectively. A significant difference in the rate of severe disease, if detected, would be an important finding.

1. To measure the prevalence of chloroquine resistant parasites during the trial, by treatment arm.

- The prevalence of parasites with the mutation *pfcrt* 76T on Day 0 of each episode of malaria

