- The prevalence of parasites with the mutation *pfcrt* 76T in cases of recurrent parasitemia after therapy

Because the genetic marker for CQ resistance is well-defined, we have the unique opportunity to assess not just resistance that is manifest on the clinical level, which may be confounded by acquired immunity, but also on the molecular level.

1. To assess the effect of each treatment arm on anemia at the end of study participation.

- Hemoglobin level without parasitemia at the close of the study

Childhood anemia is multifactorial in impoverished regions in sub-Saharan Africa and leads directly and indirectly to increased morbidity and mortality. Malaria is an important contributor to this pervasive problem (54). In our effort to simulate the public health implications of various antimalarial drug policies, we will attempt to assess the effect of each treatment arm on the general well-being of the children by measuring rates of anemia at the close of the study. We will not use the hemoglobin level at the start of the study as a point of comparison because all children will be enrolled with an episode of malaria, which will often be an acute cause of anemia. We will compare the prevalence of anemia, defined as hemoglobin <8 g/dL, at the end of one year of follow-up among all four arms.

1. To assess the safety of repeated use of the drugs in each of the study arms.

- Renal and hepatic function
- Neurological examination

Some of these medications have been associated with mild, transient abnormalities in hepatic and renal laboratory tests. We will assess these side effects in the context of repeated dosing over the course of the year. In addition, we will monitor the neurologic function of the participants due to the unique concerns associated with artemisinin derivatives.

1. To determine the chloroquine blood levels at which chloroquine sensitive and resistant parasites are able to cause infection.

- Chloroquine pharmacokinetic curve for the population
- Drug concentration at the time of parasitemia

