## Description

This study is a randomized longitudinal open-label drug efficacy trial among children who present to a government health clinic with uncomplicated falciparum malaria. Otherwise healthy children who are found to have malaria and whose parents/guardians consent to participate in the study will be enrolled in this study for one year. The participants will be randomized to one of the four drug treatment arms: CQ monotherapy, CQ plus artesunate, CQ plus azithromycin, and CQ plus AP. They will continue to receive the same treatment for each new episode of malaria for the next year. If the treatment fails, participants will receive rescue therapy, but will continue in the trial. At the first diagnosis and all subsequent new episodes of malaria, a 28 day drug efficacy study will be completed. Participants will also be asked to return for routine follow-up visit every four weeks.

***Follow-up.*** With enrollment and the first dose of therapy occurring on day 0, participants will be followed actively on days 1, 2, 3, 7, 14, 21 and 28 at the study clinic, and by daily availability of a study clinician to evaluate and treat as needed even if follow-up is not scheduled. At all active and passive follow-up times, malaria smears, hemoglobin and filter paper strips will be obtained and brief history taken and physical examinations made to seek signs or symptoms of persistent or recrudescent malaria and use of any medications outside the protocol.

In addition, participants will attend four-weekly follow-up visits at the study clinic. Weight, height, hemoglobin, temperature and malaria smears and filter papers for later evaluation of asymptomatic disease will be recorded and the participant examined and questioned for signs or symptoms of malaria or other illnesses. Further evaluation, including immediate reading of the malaria smear, will take place if the parent/guardian reports symptoms, if the participant appears ill to the clinic staff or there is a documented fever. All non-malaria illnesses will be treated according to the national guidelines.

Management of early or delayed attendance of these follow up visits is detailed in the Standard Operating Procedure.

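### Time to first resistant infection mixes infection rate with resistant share and can be misread as protection against resistance; Day-0 prevalence as worded includes pre-treatment enrolment samples

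*Protocol*

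**What the plan says.** The Rationale section of the protocol states the scientific question as "for how long does a partner drug need to be active to protect against resistance". Secondary objective 3 is to measure chloroquine-resistant parasites by arm. Section 3.2.2 gives it two outcome measures, both based on the *pfcrt* mutation: prevalence of "76T on Day 0 of each episode of malaria", and prevalence of "76T in cases of recurrent parasitemia after therapy".

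Section 11.3 (Final Analysis Plan) names one method specifically for resistance: "Survival analysis will also be used to assess time to first resistant infection in each arm". It does not mention either prevalence measure by name and does not rank the three. The protocol gives no expected resistant share, event count or sample size for this objective.

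Three other places bear on which samples count as Day 0:

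- Section 4.2 (Description): "With enrollment and the first dose of therapy occurring on day 0".
- Section 3.2.2, objective 2, where enrolment is meant to be left out: "Rate of adequate clinical and parasitologic response 28 days after subsequent new episodes of malaria".
- Section 11.3, for the primary endpoint only: "not including the first infection occurring at enrollment".

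**The concern.** Resistance can be seen only when a child has an infection to genotype. A child with fewer infections has fewer chances to show a resistant one, whatever the partner drug does to the parasites. The trial is designed around a difference in malaria incidence between arms, and the partner drugs were chosen to differ in how long they stay active. A longer time to first resistant infection could therefore reflect general prevention of malaria, a lower chance that a given infection is resistant, or both.

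The Day-0 measure raises a smaller issue. The enrolment sample is taken before any study drug, and Background Information reports that no mutant parasites have been found since 2001. If such samples are merged with follow-up samples, they form a larger fraction of the total in the arm with fewer later episodes.

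At stake is the conclusion the trial is meant to inform: which duration of partner-drug activity guards against resistance. A success on the primary endpoint could reappear as an apparent success on resistance.

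**Working it through.** The protocol has no figure of its own for the resistance analysis, so there is none to reproduce.

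**Inputs.** Section 11.2 gives the planning rates: 1.5 episodes per child-year on chloroquine alone and 1.0 on a combination, Poisson, with 120 children per arm fully observed. Follow-up is one year. Enrolment mutant prevalence is taken as 0 (Background Information). The resistant share per follow-up infection, q, is not in the protocol; it is assumed equal in both arms and varied from 1% to 50%.

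**Step 1, time to first resistant infection.** Hazard = infection rate × q, so the hazard ratio is (1.0 × q)/(1.5 × q) = 0.67 for every q. One-year risk is 1 − exp(−rate × q). The last column is the approximate chance of a two-sided p < 0.05 with 120 per arm, using D = 120 × (sum of the two risks) events and Φ(√(D/4) × ln 1.5 − 1.96) plus the small opposite tail.

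| q (assumed) | Chloroquine | Combination | Hazard ratio | Chance of p < 0.05 |
|---|---|---|---|---|
| 1% | 1.5% | 1.0% | 0.67 | 6% |
| 5% | 7.2% | 4.9% | 0.67 | 12% |
| 10% | 13.9% | 9.5% | 0.67 | 19% |
| 20% | 25.9% | 18.1% | 0.67 | 31% |
| 50% | 52.8% | 39.3% | 0.67 | 57% |

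A simulation with 120 per arm and 3,000 trials at each of q = 5%, 10%, 20% and 50% gave hazard ratios of 0.65 to 0.67 and rejection rates of 12%, 18%, 31% and 56%.

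**Step 2, dependence on the rates.** With 1.5 episodes in both arms the ratio is 1.00. With 1.25 in the combination arm it is 1.25/1.5 = 0.83. Conversely, if the combination arm has 1.0 episodes but a share of 1.5q, the ratio is (1.0 × 1.5q)/(1.5 × q) = 1.00, and the higher share does not show.

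**Step 3, Day-0 prevalence if pooled over all episodes.** Each child contributes one enrolment sample and, on average, *rate* follow-up samples. Prevalence = rate × q/(1 + rate).

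- Chloroquine: 1.5q/2.5 = 0.60q; enrolment samples are 1/2.5 = 40% of the total.
- Combination: 1.0q/2.0 = 0.50q; enrolment samples are 1/2.0 = 50%.
- Ratio: 0.50/0.60 = 0.83. At q = 5% this is 3.0% against 2.5%.
- With 1% mutants at enrolment the ratio is 0.88 at q = 5% (3.0%/3.4%) and 0.85 at q = 20% (10.5%/12.4%).

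**Step 4, measures that separate the two mechanisms.** The share among follow-up infections alone is q in both arms, ratio 1.00. The hazard ratio for first chloroquine-sensitive infection is 1.0(1 − q)/1.5(1 − q) = 0.67, the same as the resistant one. Equality of the two ratios shows that only the infection rate differs.

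**The case against.** **The protocol already has an unaffected measure.** A reader might infer from 11.3 that incidence and resistance cannot be told apart. That goes too far. Prevalence in "76T in cases of recurrent parasitemia after therapy" has a post-treatment, per-infection denominator and gives a ratio of 1.00 in the scenario above. What remains is that 11.3 neither names it nor gives it priority. It may also be sparse if recurrence means within the 28-day follow-up: in the 2005 study (Table 1) none of the 80 chloroquine children with a known outcome (105 − 25) had a late failure.

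**Pooling is not stated.** A reader might take the Day-0 measure to be one merged figure per arm. The wording supports including enrolment, but a tabulation by episode, with enrolment as the first row, is equally compatible and would avoid the dilution. This objection stands: step 3 is conditional.

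**Incidence of resistant infection is a legitimate estimand.** The comparison is randomised, and a partner drug that prevents resistant and sensitive infections alike does leave children with fewer resistant infections. This also stands. The fault lies in reading the result as less selection for resistance, not in the analysis itself.

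**The resistant share has its own weakness.** It conditions on having an infection after randomisation, which treatment affects. A drug that prevents only sensitive infections raises the share without adding a resistant infection, so the higher share in step 2 is not by itself evidence of harm. For the same reason a rule that grants protection only when the resistant ratio is below the sensitive one would be too rigid: it would deny any benefit to a drug that cuts both equally.

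**The 0.67 is scenario-specific.** It takes clinical episodes as the infections. Section 4.2 also collects filter papers for asymptomatic infection, and 11.3 does not limit a resistant infection to clinical cases, so the relevant rate ratio may differ.

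**Conclusion.** The concern holds in a limited form. Time to first resistant infection measures resistant infections per child. Under the protocol's own design alternative and an equal resistant share, it gives a hazard ratio of about 0.67 with no difference in resistance per infection. The shift is the ratio of infection rates and disappears when the rates are equal.

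It does not follow that an arm with fewer episodes will always look protective. At a share of 5% or less, a falsely significant result is unlikely (about 6% to 12% against a nominal 5%), although the estimate is still shifted. The Day-0 ratio of 0.83 rests on pooling that the protocol does not specify and on about 0% mutants at enrolment. The resistant share is an assumption throughout.

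This is a secondary objective, but it carries the question in the Rationale, so clarifying it is worthwhile.

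**What to change.** In 3.2.2 and 11.3:

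1. Use the enrolment Day-0 *pfcrt* result as baseline only.
2. Compare arms on the share of post-enrolment infections carrying 76T, allowing for repeated infections in the same child.
3. Label time to first resistant infection as a measure of incidence.
4. Report beside it the hazard ratio for first chloroquine-sensitive infection, and interpret the two together without a fixed rule for claiming protection.

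The cost is wording; the specimens are already planned. The prevalence comparison will rest on fewer samples, though those removed predate treatment and say nothing about its effect. Because the resistant share depends on who becomes infected after randomisation, it should be read with the two hazard ratios and not alone.

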# Assessment of Safety

## Specification of Safety Parameters

Complete blood count, ALT and creatinine will be measured every time an episode of clinical malaria occurs, at day 14 after the treatment and at approximately 3-month intervals (see study schedule). An age-appropriate neurological examination will be conducted after resolution of the initial illness, at two regular intervals, and at the last visit of the study.

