Appendix III: Use of normal and abnormal values

Normal values for hematological and biochemical evaluations from healthy children in rural Mozambique (Quinto, et al. Tropical Medicine and International Health submitted, 2006) were used to define abnormalities in hemoglobin, ALT and creatinine.

ALT> 300IU/L is greater than 5 times the upper limit of normal

Creatinine>140 mol/L is greater than 3 times the upper limit of normal.

|  | Grade 1 | Grade 2 | Grade 3 | Grade 4 |
| --- | --- | --- | --- | --- |
| **Hemoglobin for children less than or equal to 3 years of age** | 6.6-6.9 g/dL | 6.0-6.5 g/dL | <6.0 g/dL | Cardiac Failure secondary to anemia or requiring a transfusion |
| **Hemoglobin for children greater than 3 years of age** | 7.6-7.9 g/dL | 7.0-7.5 g/dL | <7.0 g/dL | Cardiac Failure secondary to anemia or requiring a transfusion |
| **ALT (IU/L)** | 75-150 | 151-300 | 301-600 | >600 |
| **Creatinine mol/L** | 50-70 | 70-140 | 141-280 | >280 |

Other laboratory abnormalities will be graded according to the DMID Pediatric Toxicity Tables:

[http://icssc.org/documents/AE%20Manual%202003%20Appendices%20February_06_2003%20final.pdf](http://icssc.org/documents/AE Manual 2003 Appendices February_06_2003 final.pdf). Attached below

|  | Grade 1 | Grade 2 | Grade 3 | Grade 4 |
| --- | --- | --- | --- | --- |
| **Neutrophil count** | 750-1200/mm3 | 400-749/mm3 | 250-399/mm3 | <250/mm3 |

[figure not shown]

[figure not shown]

[figure not shown]

[figure not shown]

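### The only between-arm method named for renal and hepatic function is chi-square on toxicity episodes, which is much less powerful for a small general shift than comparing the ALT and creatinine values the trial collects

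*Protocol*

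**What the plan says.** Section 3.2.2 gives the outcome for objective 5 as "Renal and hepatic function", together with the neurological examination. The reason given is: "Some of these medications have been associated with mild, transient abnormalities in hepatic and renal laboratory tests". It continues: "We will assess these side effects in the context of repeated dosing over the course of the year".

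On timing, section 9.1 states: "Complete blood count, ALT and creatinine will be measured every time an episode of clinical malaria occurs, at day 14 after the treatment", and then roughly every three months. Section 7.3 and Appendix I put the routine draws at visits 4, 8 and 13.

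The analysis is in section 11.3: "Categorical data including episodes of liver, kidney or neurological toxicity and presence of anemia will be compared using" chi-square (the Greek letter is lost in the text, but the meaning is clear). It adds: "Logistic regression will be used to adjust for covariates".

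Appendix III sets the grades. For ALT the bands for Grades 1 to 4 are "75-150 | 151-300 | 301-600 | >600" IU/L, and "ALT> 300IU/L is greater than 5 times the upper limit of normal". Section 11.3 does not say which grade makes an episode, or whether the unit counted is the child or the episode.

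**The concern.** The outcome is organ function measured on a continuous scale, and the anticipated effects are described as mild. Both methods named are binary. If a drug raises ALT or creatinine slightly in most children, few of them cross a toxicity cut, and a comparison of counts has little chance of showing it.

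The wording also counts episodes. ALT and creatinine are drawn at the start of every malaria episode and 14 days after treatment, so an arm with more malaria is tested more often. A chi-square on episodes would also treat repeat results in one child as independent.

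What is at stake is a weak or falsely reassuring safety comparison. This matters most for chloroquine plus atovaquone-proguanil, which the background section says had not been studied in vivo.

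**Working it through.** **1. The plan's own figures.** The protocol gives no power or precision for ALT or creatinine, so I checked the two figures that it does give in section 11.2.
- Primary sample size, 1.5 vs 1.0 episodes a year, two-sided alpha 0.05/3, 90% power: [2.394·√(2/1.5) + 1.282·√(1/1.5 + 1/1.0)]² / (ln 1.5)² = 118.8, so 119 per arm (stated: 120).
- Anemia half-width: 1.96·√(2·0.2·0.8/120) = 0.101 (stated: about 0.10).

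Both reproduce. I use 120 per arm below.

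**2. Where the cuts lie (Appendix III).** The ALT upper limit is 300/5 = 60, so Grade 1 starts at 75/60 = 1.25 times that limit. The creatinine upper limit is 140/3 = 46.7, so Grade 1 starts at 50/46.7 = 1.07 times.

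**3. One value per child.** Assumptions: normal values on the log scale, a uniform shift of d SD, a proportion p0 of controls above the cut, two-sided 0.05. With z = Φ⁻¹(1 − p0), the shifted arm exceeds the cut with probability p1 = 1 − Φ(z − d). The t-test has noncentrality d·√(120/2).

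Example, d = 0.35 and p0 = 2.5%: p1 = 1 − Φ(1.96 − 0.35) = 5.4%, which is about 6.4 children against 3.0. Chi-square power is 19%. The t-test noncentrality is 0.35·√60 = 2.71, giving 77%.

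| Shift (SD) | Chi-square, p0 0.5-2.5% | Log-scale comparison |
|---|---|---|
| 0.25 | 2-11% | 49% |
| 0.35 | 4-19% | 77% |
| 0.50 | 11-40% | 97% |

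If 10% of controls exceed the cut, chi-square power at 0.35 SD is about 40%.

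**4. Five values per child.** Children are tested repeatedly, so any exceedance during the year is commoner than the table suggests. Five is a realistic count: one enrolment day 14, three routine visits, and 1.0 to 1.5 later day-14 draws make 5.0 to 5.5. Simulation with an assumed within-child correlation of 0.3 to 0.5, comparing any exceedance with the child mean:

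| Shift (SD) | Chi-square, 0.5-2.5% above cut per test | Child means |
|---|---|---|
| 0.25 | 12-31% | 69-83% |
| 0.35 | 20-59% | 93-99% |
| 0.50 | 46-90% | over 99% |

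The gap narrows but does not close.

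**5. Which grade counts.** Assume log-normal ALT, control median 15 to 30, the upper limit at the 97.5th percentile, and one value per child. A 25% rise then has 12-25% chi-square power at Grade 1 or higher and 3-4% at Grade 2 or higher. The continuous comparison has 69-99.8%.

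**6. Unequal testing.** At the planned rates, day-14 draws number 1 + 1.5 = 2.5 per child on monotherapy and 1 + 1.0 = 2.0 on a combination. Adding the three routine visits gives 5.5 against 5.0. If day-0 draws of later episodes also count, it is 7.0 against 6.0.

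**7. A different kind of effect.** If instead 10% of children have a rise of 3 SD (one value each), chi-square power is about 77-84% and the mean comparison about 49%. The ranking reverses.

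**The case against.** Section 11.3 says how categorical data are tested. It does not say that ALT and creatinine will be analysed only as categories, and a separate statistical analysis plan may add a continuous analysis. That stands. A reader might infer that the protocol rules out a continuous comparison, and the text does not support this. The narrower point survives, because the protocol does name a method for this outcome and the method named is binary.

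The protocol speaks of mild abnormalities, which can be read as threshold events, and Grade 1 starts just above normal. A reader might infer that the effect sought is a mean shift and that it would be almost undetectable. Neither follows. The shift is one reading of the aim. Near-zero power holds for Grade 2 or higher or for rare Grade 1 events, but not generally: a 50% ALT rise has 34-79% power at Grade 1 or higher under the assumptions of step 5, and repeated testing raises power further.

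The background section reports that atovaquone-proguanil transaminase rises in Thai adults had evened out with the other arms by day 14. Day 14 is the first scheduled ALT after dosing. If that pattern holds here, neither method will see that rise, and the continuous powers above do not apply to it.

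The protocol also does not say that the day-0 value is left out, since it does not list the covariates. Nor does it say that a non-significant test would be reported as no effect. Adverse event grading, the independent safety monitor and the DSMB provide safety review apart from this test.

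**Conclusion.** The point holds in limited form. For a small shift across most children, the only between-arm method named is substantially less powerful than a comparison of the measured values: about 2-40% vs 49-97% with one value per child, and about 12-90% vs 69-100% with five. These figures rest on assumed shifts of 0.25 to 0.5 SD, 120 children per arm, two-sided 0.05, and a cut exceeded by 0.5 to 2.5% of controls per test. The protocol gives no SD, expected shift or toxicity rate, so none of these assumptions can be checked against it.

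Counting by episode adds a second weakness, because testing opportunity follows the primary outcome. The advantage is not universal: graded counts do better when a minority of children have large rises, so they should remain a compared endpoint. This is a worthwhile improvement to a secondary safety objective.

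**What to change.** In section 11.3, beside the graded-toxicity comparison, add a between-arm comparison of log ALT and log creatinine at the times scheduled equally for every arm: day 14 of the enrolment episode and visits 4, 8 and 13. Adjust for the enrolment day-0 log value, include a child random effect, and report geometric-mean ratios with 95% confidence intervals for each combination against monotherapy.

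Compare graded toxicity per child (any event, with the grade named) rather than per episode. This removes the dependence between repeat results in one child. Showing it also for the equally scheduled times alone would remove the unequal testing.

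Label as exploratory any model that uses cumulative treatment courses or values from later episodes. Both arise after randomisation, the number of courses is close to the primary outcome, and a later day-0 value may already carry the drug effect sought.

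The cost is protocol or analysis-plan wording and a modest amount of analysis, with no new samples. A mean shift has to be read beside the graded counts to judge whether it matters clinically.
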